## Abstract

**Background:**

There is international interest in whether improved primary care, in particular for patients with chronic or complex conditions, can lead to decreased use of health resources and whether financial incentives help achieve this goal. This trial (EQuIP-GP) will investigate whether a funding model based upon targeted, continuous quality incentive payments for Australian general practices increases relational continuity of care, and lessens health-service utilisation, for high-risk patients and children.

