### Objectives

The study aims to evaluate the impact of a new funding model in primary care, comprising targeted incentives for enrolment with a preferred provider, longer consultations, same day access and structured follow-up after hospitalisation, on the quality of care and health service utilisation, and related costs for patients at increased risk of hospitalisation. The impact of the intervention will be compared to usual care.

The funding model trial will test incentives for specific quality improvement factors in high-risk chronic disease populations and provides payment incentives that are proportional to the expected health system cost savings resulting from those patients’ care improvement. This model enables incentives for continuous quality of care improvement within existing overall health system budgets, rather than previous quality incentive models with fixed block payments at target thresholds having localised incentives and without budgetary justification [17–19].

The primary hypothesis is that among high-risk patients and children attending general practices, the introduction of a practice-level service model incorporating continuous and graded quality improvement incentives, will improve patient-perceived relational continuity. Our specific research questions are:In patients over the age of 65 living with chronic illness, what is the impact of an incentivised practice-level service model promoting access to preferred primary care providers, longer consultations and structured post-hospitalisation follow-up on:patient-perceived relational continuity of care;referrals for specified radiology and pathology services;medicine prescriptions;potentially avoidable hospitalisations (PAHs); andemergency department attendances.Does the application of this model in patients under 16 years of age (with defined comorbidities) provide improved access to same day care?Is the model cost-effective when used in each population?How acceptable is the model for patients and staff members of primary care practices?

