**Fig. 2 Fig2:**
[figure not shown]
Plain language incentive structure (as provided to participating general practices)

An intervention facilitator (IF) will be employed by each of the three collaborating centres. They will work with practices in the intervention arm of the study to facilitate implementation of the new service model. They will also collect data relevant to their facilitator role using structured diary keeping. These diaries will contribute data concerning practice culture, communication and routines, plus information about the challenges and successes of the intervention. The EQuIP-GP Trial timeline is summarised in Table 2.

**Table 2 Tab2:** EQuIP-GP Trial timeline

Task Name	Start	Finish
*Practice Recruitment*	April 1 2018	November 30 2018
○ Publicity will be communicated through the PBRN newsletter and/or blog posts		
○ After publicity appears, all practices in the three PBRN’s will be sent a letter, information sheet and consent form.		
○ Practices expressing interest will receive a visit from investigators or a research staff team member to facilitate a more detailed discussion of the study.		
Practice Randomisation ○ Dynamic randomisation of practices will occur after consent has been gained by practices.		
Data collection ○ Distribution of pre-trial provider and facility surveys to practices		
○ A sample of consenting practice staff will be contacted directly by the research team to arrange qualitative interviews following randomisation		
*Patient Recruitment*	June 1 2018	December 31 2018
○ A Practice Nurse in the consenting practices will run an electronic search of the patient database in order to identify potential participants who meet the inclusion criteria		
○ A sample of 200 patients identified in the electronic search will be sent an information pack containing a letter of invitation, an information sheet and a consent form. ○ After 2 weeks, if recruitment is insufficient, then direct invitation to patients presenting to the practice will commence		
Baseline data collection ○ Distribution of pre-trial patient surveys: PCAT, EQ-5D-5 L HRQOL and ease of access survey to parents/guardians of <16 patients.		
○ A sample of consenting patients will be contacted directly by the research team to arrange qualitative interviews following recruitment.		
*Intervention period*	August 1 2018	July 31 2019
Intervention facilitation		
○ Intervention facilitators to visit intervention GP practices 3 times	August 1 2018	January 31 2019

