### Standard care

Control practices will provide usual care. Usual care in the context of this study is care received by patients in daily practice in regard to their particular health concerns [21], and represents normal practice against which to compare the intervention.

Both intervention and control practices will be provided access to links to quality improvement education materials (e.g. including Choosing Wisely Australia recommendations for improving the quality of healthcare by eliminating unnecessary and sometimes harmful tests, treatments, and procedures [33]).

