### Health economic evaluation

The payment model has been designed following the net benefit correspondence theorem (NBCT) [17–19, 44] to create continuous quality of care improvement incentives with a conservatively health system budget neutral mechanism; with quality of care incentive payments relative to expected downstream cost savings from improved quality. The NBCT provides a generalised method to enable appropriate incentives for improving health system performance, which, as in hospital applications [17, 19], has robust coverage and comparability conditions to create appropriate accountability and prevent perverse incentives - cost and effect shifting and cream skimming.

Importantly, as quality improvement incentives are conservatively budget neutral or potentially somewhat cost saving to the health system, if the trial finds they are effective in improving quality of care relative to usual care, the mechanisms design provides for strong policy-relevant integration into current practice in a health system budget-constrained environment.

Generalisability, implementation and scalability of any such trial findings from case control analysis will be aided by triangulation with qualitative research and pre-post analysis of impacts in the intervention arm, with particular consideration of barriers and enablers to study findings.

The health economic analysis of trial outcomes will jointly consider the health effects and net costs, including downstream health system (prescribed medication and hospital) costs of a capitation-based GP payment system, where bonus payments are continuous across specified ranges for quality of care measures for each of the activities proposed [17–19, 45].

Analysis with patient level data will include representing joint cost and effect distributions on the cost-effectiveness plane (two strategy comparisons), cost-disutility plane (multiple strategy comparisons) and relevant summary measures. These summary measures include internationally recognised best practice measures of the level of the probability of, and expected gain from, being cost-effective: net benefit and cost-effectiveness acceptability curves for two strategy comparison [46]; expected net loss curves and frontiers for multiple strategy comparisons [17, 18, 45], and expected net loss planes and surfaces with multiple domain of effect comparisons [17, 44].

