## Discussion

This trial consists of a practice-based intervention implemented in the primary care setting and predominantly using quantitative data collection and analysis. The trial is designed to test the effects of a new funding model that provides financial incentives for continuous quality improvement in general practice, proportional to the expected downstream cost savings. As part of the trial design, nested case studies are planned. These are intended to contextualise the quantitative findings and provide insights into the attitudes and beliefs of patients and practitioners, and their perceptions about the success or otherwise of the intervention.

The development of the intervention was underpinned by several key tenets, namely that:high-quality primary health care can reduce the use of secondary care, thus reducing health system costs;the design and use of financial models that support high-quality primary care are crucial to the uptake of quality improvement activities and better patient outcomes; andfinancial incentives for quality improvement are more likely to succeed when incentives are continuous and targeted to specific tasks that are closely linked to high-quality care.

Thus, the trial was designed to incentivise GPs to provide enrolled patients with longer consultations, same day access and rapid follow-up after hospitalisation, and to achieve associated quality improvements linked to these tasks. The primary outcome measure of the trial is patient-perceived relational continuity and secondary outcomes include changes in pathology and imaging, total prescriptions and rates of PAHs - all indicators of quality of care.

The design of funding models to support high-quality primary care is crucial to the uptake of quality improvement activities and better patient outcomes [48]. Health economic theory suggests that incentives with GP payments based on fee-for-service can be significantly improved with capitation payments conditional on continual quality improvement [49–54]. Indeed, our review of international financial models for effective primary care indicated that a blend of fee-for-service, capitation and pay-for-performance elements appeared to provide the best balance between improved patient outcomes and productivity. However, the evidence strongly suggested that the incentives were only successful when targeting tasks closely linked to professional standards of high-quality care [48].

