We are using an embedded mixed methods design to incorporate a qualitative component into an outcomes-based randomised controlled trial. This qualitative data will be used to develop understanding of how the intervention is experienced by participants, and to help contextualise and explain the quantitative results. Our analysis aligns with Creswell and Plano Clark’s model of mixing data using embedded mixed method design [58]. At a pragmatic level, we anticipate that by integrating the embedded qualitative component with our quantitative trial data we will better be able to:reveal and contextualise relationships between variables and outcomes;explore and possibly explain differences in effect size;assess the acceptability of the trial model from multiple perspectives; andprovide insight into discrete, potentially unanticipated impacts of the model on patients and practitioners.

The trial is designed to generate robust, policy-relevant evidence of the impact of a new service model of primary care practice, comprising targeted practice incentives for patient enrolment with a preferred provider, longer consultations, same day access and structured follow-up after hospitalisation, on the quality of primary care and health service utilisation for patients at increased risk of hospitalisation. In addition, the trial will provide evidence on continuous quality improvement incentives which can be compared to block funded pay-for-performance models in the UK [59], the patient-centred medical home model in the United States [60] and the Australian Government ‘Health Care Homes’ trial [31].

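### The trial compares a facilitated incentive package with usual care, but the aim, the Discussion and above all the economic section credit the result to the incentives

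*Protocol article*

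**What the plan says.** The protocol article states the object of the test in several places.

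- Abstract, Background: the trial will "investigate whether a funding model based upon targeted, continuous quality incentive payments for Australian general practices increases relational continuity of care".
- Objectives, aim sentence: "The study aims to evaluate the impact of a new funding model in primary care, comprising targeted incentives for enrolment with a preferred provider". The list goes on to longer consultations, same-day access and follow-up after hospitalisation. Facilitation is not in it.
- Discussion, opening paragraph: "The trial is designed to test the effects of a new funding model that provides financial incentives for continuous quality improvement in general practice".
- Discussion, closing paragraph: "the trial will provide evidence on continuous quality improvement incentives which can be compared to block funded pay-for-performance models".
- Health economic evaluation: the quality incentives are described as conservatively budget neutral or possibly cost saving, and "if the trial finds they are effective in improving quality of care relative to usual care", their design is said to support integration into policy within a constrained budget. The word *they* refers to the incentives.

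On what the arms receive, the Intervention section says of the facilitators employed by the three centres: "They will work with practices in the intervention arm of the study to facilitate implementation of the new service model". Table 2 gives three visits between August 2018 and January 2019. Under Standard care: "Control practices will provide usual care". The only support given to both arms is links to education materials.

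The primary hypothesis in Objectives is worded differently. It concerns a practice-level service model that incorporates the incentives.

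**The concern.** The facilitator goes to one arm only, and the protocol does not treat the role as inert. The Overview makes facilitation one of three principles behind the work and describes it as overcoming obstacles to evidence-based care and inefficiencies in practice routines. Better routines could improve access and continuity without any payment.

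If a positive result is reported as the effect of the incentives, a payer may adopt the payments without the facilitators and expect the trial's effect. The economic section invites this reading. It takes effectiveness from a contrast that includes facilitation and takes affordability from an argument about payments alone.

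**Working it through.** The point rests on no stated figure, so the check sets the arms and the claims side by side.

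**1. What each arm receives**

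| Component | Intervention | Control | Where stated |
|---|---|---|---|
| Incentive payments | yes | no | Intervention |
| Service model (enrolment, longer appointments, post-hospital review, same-day access for children) | yes | no | Intervention |
| Facilitator, three visits | yes | no | Intervention; Table 2 |
| Links to education materials | yes | yes | Standard care |

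**2. What the contrast identifies**

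Let *I* = 1 if the practice has the incentive service model and *F* = 1 if it has a facilitator. The trial observes only the cells (*I*, *F*) = (1, 1) and (0, 0).

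Difference between arms = effect of *I* alone + effect of *F* alone + their interaction.

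That is one estimable quantity and three unknowns. The effect of incentives without facilitation needs the cell (1, 0), and the effect of facilitation without incentives needs the cell (0, 1). Neither exists. The analysis can estimate the sum but cannot divide it.

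**3. Timing**

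Incentives are calculated and paid at the end of the 12 months. Table 2 places facilitator visits in the first six months and the follow-up survey that carries the primary outcome in July and August 2019, around the end of the intervention on 31 July 2019. The payments can therefore act on that outcome mainly through expectation, whereas facilitation has been delivered well before it is measured. This does not show that facilitation is the cause. It shows that facilitation cannot be set aside as negligible.

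**4. What the budget argument covers**

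The neutrality argument compares two quantities: payments ≤ downstream savings.

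The savings that the trial could show would be those obtained with facilitation. For the package as delivered, the matching condition is: payments + facilitation cost ≤ downstream savings.

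The first condition can hold while the second fails. If savings exactly equal payments, the package has a net cost equal to the cost of facilitation. The text of the article gives no amount for any of the three terms, so the gap cannot be sized.

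**5. Which statements fit the contrast**

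The primary hypothesis and the service-model sentence in the closing paragraph of the Discussion are near to the package, although neither names facilitation. The abstract's background, the aim sentence, the opening of the Discussion, the sentence on evidence about incentives and the economic inference do not fit it.

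**6. Power**

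The stated 98% power, for a difference of 0.2 in adults with an ICC of 0.05, refers to the comparison between the randomised arms. Renaming that comparison changes none of its inputs.

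**The case against.** The strongest reply is that this is a declared pragmatic trial of a complex intervention, and a package against usual care is the ordinary contrast for such a trial. The facilitator's stated job is to help practices put the model in place, so the role can be seen as delivery of the model and not as a rival treatment. The abstract's methods disclose the facilitator openly. The hypothesis under test speaks of a service model. Facilitator diaries, facilitator interviews and the realist analysis are planned to examine how the model worked, and the economic section says that judgements on scale-up will draw on qualitative work.

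Most of this stands, and it sets the limits of the point. The design is legitimate and the comparison between arms is valid for what it compares. But the qualitative interviews are confined to intervention practices and the diaries come from facilitators who work only there, so they can describe the part that facilitation played but cannot separate its effect. Disclosing the facilitator in the methods also does not correct the sentences that attribute the result to the incentives.

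Three stronger readings are tempting and are not supported.

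- A reader might infer that facilitator cost is left out of the economic analysis. The net-cost sentence gives its items as an open list, the Overview promises to study the resource use and costs of the service model, and an itemised costing may stand in a fuller document. What is established is only that the neutrality argument does not mention facilitation.
- A reader might infer that a randomised comparison with block payments is claimed. The text says only that the evidence can be compared with such schemes, and the programmes it names are external.
- A reader might infer that the trial is underpowered for the incentives. Any such figure needs an assumed split of the effect, which the document does not give, and the 98% is not stated for an incentives-only contrast.

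**Conclusion.** The point holds as one of attribution. The trial estimates the effect of the incentive service model with outreach facilitation against usual care. Several statements credit that effect to the funding model or the incentives, and the economic section pairs it with a neutrality argument that covers the payments only. The share due to the incentives could be anything from none to all of the effect, and these two arms cannot narrow that range. The conclusion assumes only what the protocol says: facilitation goes to one arm and is expected to change how practices work. No outcome, sample size or primary analysis is called into question. The correction is worth making because it changes what a positive result entitles the investigators to conclude.

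**What to change.** Keep the design.

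1. In the abstract's background, the aim sentence and the opening and closing paragraphs of the Discussion, state the randomised contrast as the incentive model with outreach facilitation against usual care.
2. In the Health economic evaluation, limit the effectiveness and budget-neutrality inference to that package.
3. State that facilitator cost is counted in the intervention arm's net cost as the base case, and show a scenario without it as secondary. If a fuller document already provides for this, a sentence confirming it is enough.

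The cost is some rewording and one cost item, which should be within reach because the collaborating centres employ the facilitators. The downside is a narrower policy claim and a slightly less favourable net cost.

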### Trial status

The trial is ongoing, with patient recruitment commencing June 1 2018 and completed December 31 2018 and trial completion July 31 2019. The study was in in the intervention and data collection stages at the time of the protocol manuscript submission.

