### Intervention

Intervention general practices will be supported to implement a new service model incorporating quality incentives for patients’ relational continuity and timely access. The intervention itself will comprise a mechanism of, firstly, patient enrolment within a practice. The practice will then offer enrolled patients: a) guaranteed access to a minimum of three longer appointment types over the study period for older patients or those with chronic or complex illness; b) a review visit within 7 days of admission to an emergency department or hospital, or after other significant health events; and c) for patients aged less than 16 years, same day access for acute conditions.

Figure 2 summarises the incentive structure. All incentives are calculated over the 12 months of the trial and compared with the 12-month period immediately previous to the trial. The incentive payments apply to the percentage of change achieved across the group of enrolled patients at the level of the practice. The incentives supplement the existing payment arrangements. All incentives will be calculated and paid at the conclusion of the 12-month trial.

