Follow-up data collection	July 1 2019	August 31 2019
○ A sample of consenting practice staff will be contacted directly by the research team to arrange follow-up qualitative interviews.		
○ Distribution of post-trial patient surveys: PCAT, EQ-5D-5 L and ease of access survey to parents/guardians of <16 patients.		
○ A sample of consenting patients will be contacted directly by the research team to arrange qualitative interviews.		
○ Intervention facilitator interviews		
○ Electronic Health Record data extraction for period August 1 2017 – July 31 2019		

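### One fixed intervention year overlaps recruitment by four to five months, so the stated 12-month trial period fails for late entrants and some survey baselines may fall after the start

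*Protocol article*

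**What the plan says.** Table 2 (trial timeline) fixes three windows:

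- practice recruitment, "April 1 2018 November 30 2018"
- patient recruitment, "June 1 2018 December 31 2018"
- the intervention period, "August 1 2018 July 31 2019"

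The intervention window is a single calendar year. No practice-specific start and no extension for late entrants is given. Trial status repeats the recruitment and end dates ("patient recruitment commencing June 1 2018 and completed December 31 2018 and trial completion July 31 2019"), so they are not a slip confined to the table.

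On allocation, Table 2 says "Dynamic randomisation of practices will occur after consent has been gained by practices". The section on randomisation confirms that practices are allocated one by one as they consent, and the section on patient recruitment places the patient search after allocation. Table 2 lists the baseline PCAT, EQ-5D-5L and access surveys, labelled pre-trial, under the patient recruitment task, which runs to the end of December. The row "Intervention facilitators to visit intervention GP practices 3 times" starts on 1 August 2018. Follow-up data collection runs from 1 July to 31 August 2019.

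For service use and payment, the Intervention section says "All incentives are calculated over the 12 months of the trial and compared with the 12-month period immediately previous to the trial". The Outcomes section uses the same pair of 12-month periods, and Table 2 specifies "Electronic Health Record data extraction for period August 1 2017 – July 31 2019". The primary outcome (Quantitative data analysis) is the between-group difference in change in PCAT relational continuity from baseline to trial completion.

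**The concern.** The protocol describes a 12-month trial period set against the 12 months before it. Its own dates allow that only for practices and patients in place by 1 August 2018. Later entrants are affected in two ways.

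**Service use and incentive payments.** The fixed window counts months before a late practice was allocated as trial months. No effect can arise in those months, so the before-and-after contrast in the intervention arm is diluted. The percentage change on which payments rest is diluted in the same way.

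**Surveys.** In an intervention practice randomised early, facilitation can begin in August while patients are still returning baseline forms up to December. A baseline taken after the practice has changed its behaviour already contains part of the effect, which shrinks the measured change in that arm. In a practice randomised late the baseline may be clean, but exposure before follow-up is short. For a given patient these are mainly alternatives and should not simply be added together.

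**Working it through.** **Inputs.** All dates are from Table 2 and Trial status. The 0.2-point effect, 98% power and ICC of 0.05 are from Sample size and power, which states neither an SD nor a significance level.

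**1. The protocol's own figure.** 1 August 2018 to 31 July 2019 inclusive is 365 days. As a calendar window, the 12 months reproduces.

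**2. Overlap with recruitment.**
- Practices: 1 August to 30 November 2018 = 31 + 30 + 31 + 30 = 122 days. The recruitment window from 1 April is 244 days, and 122/244 = 50%.
- Patients: 1 August to 31 December 2018 = 122 + 31 = 153 days. The recruitment window from 1 June is 214 days, and 153/214 = 71%.

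**3. Time left for the last entrant, to 31 July 2019.**
- Practice entering 30 November 2018: 243 days, 243/30.44 = 8.0 months.
- Patient entering 31 December 2018: 212 days, 212/30.44 = 7.0 months.

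**4. Survey interval for the last patient.** From 31 December 2018 to a follow-up form between 1 July and 31 August 2019 is 182 to 243 days, about 6 to 8 months.

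**5. Pre-allocation time counted as trial time.** A practice allocated on 30 November 2018 has 121 days from 1 August to 29 November before allocation, and 121/365 = 33%. A constant effect after allocation would appear in the window average at 244/365 = 67% of its size. This is the extreme case. A practice allocated by 1 August has none.

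**6. Is there a service-use baseline?** Yes. The health record extract opens on 1 August 2017, and Table 3 lists previous-12-month values for the MBS, PBS and state hospital sources. The year 1 August 2017 to 31 July 2018 precedes the intervention for every patient. The baseline question therefore concerns only PCAT, EQ-5D-5L and the access survey.

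**7. Illustration of power.** Assume that patients enter uniformly from 1 June to 31 December 2018, that the effect is proportional to exposure, and that the test is two-sided at 0.05.
- The 61 days before August give 365 days of exposure each. The 153 days from August give 365 falling to 213 (entry day included), mean 289.
- Mean exposure = (61 × 365 + 153 × 289)/214 = 310.7 days, or 10.2 months. As a fraction of the year, f = 310.7/365 = 0.851.
- The effect becomes 0.2 × 0.851 = 0.17.
- 98% power implies a standardised effect of 1.960 + 2.054 = 4.014, whatever the SD. Power = Φ(4.014 × 0.851 − 1.960) = Φ(1.456) = 0.93.
- If every patient had only 7 of 12 months, power = Φ(4.014 × 7/12 − 1.960) = Φ(0.38) = 0.65. That is a bound, not an expectation.

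**The case against.** The strongest defence is that the calendar window is common to both arms, patients are identified and invited in the same way in both, and the primary contrast is defined at trial completion, not 12 months after each entry. A common August-to-July year also matches the seasons before and after. All of this stands. The randomised comparison remains valid, and what it estimates is an effect over a shorter average exposure.

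A reader might go further and infer that late entrants have no pre-intervention baseline at all. The documents do not support that. Service use has one for everyone. For an individual patient the intervention begins with enrolment in the practice, so a survey completed in December can still precede that patient's own exposure. A contaminated survey baseline is possible and not excluded by the text, but it is not established and does not apply to every late entrant.

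A reader might also infer that the result could not be interpreted, or that power falls to 65%. Dilution towards no effect is not loss of meaning, and the 65% needs every patient to enter on the last day. Even the 93% rests on uniform entry and a linear effect, neither of which is in the protocol.

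The defence does not remove the mismatch itself. The 12-month and pre-trial labels do not fit the protocol's own dates.

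**Conclusion.** The point holds in a limited form. By the protocol's own dates, the 12-month trial period does not apply to late entrants: the last practice can have about 8 months and the last patient about 7. Service-use comparisons and incentive calculations include up to 33% pre-allocation time for the latest practice and less for others. Survey baselines in early-randomised intervention practices can fall after the start, which would shrink the measured change in that arm.

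If the intervention works, the bias is towards no effect. Its size depends on the actual entry dates, which the protocol does not report. The fall from 98% to about 93% power is illustrative only. What does not depend on assumptions is the date arithmetic and the need to reconcile the recruitment windows, the intervention window and the two labels.

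**What to change.** Recruitment had closed and the trial was in its intervention stage when the article was submitted, so the remedy lies mainly in the analysis and the wording.

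1. Define a start date for each practice by the same rule in both arms: the later of 1 August 2018 and the allocation date. The allocation date alone would not do, because practices allocated from April would then have pre-August time counted as intervention time.
2. In the service-use and mortality analyses, count only person-time after that date, with an offset for its length. For mortality, do not start the count before the patient's consent, since a late recruit must have survived until then.
3. Classify each PCAT baseline as before or after the practice start and adjust the primary model for the time between surveys. Add a sensitivity analysis that treats baselines after the start as missing in both arms. Apply the same classification to EQ-5D-5L and the access survey.
4. Replace 12-month by the actual exposure range, about 7 to 12 months, and reconcile the incentive window with it.

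The cost is modest extra analysis, some loss of the seasonal match for late practices, and a less favourable stated exposure. The incentive basis has already been given to practices, so any change to it must be communicated. No extra patients are needed.
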